### Assessments

Participant self-reported data will be collected at baseline, 6 months, 12 months and 15 months (post-randomisation):

Demographics (baseline only).The EQ-5D-5L (EuroQol-5 dimensions-5 levels) questionnaire, a validated generic patient-reported outcome measure.^51^Symptom assessment with the Seattle Angina Questionnaire.Psychological well-being assessment with the Hospital Anxiety and Depression Scale (HADS).Holistic capability assessment with the ICEpop CAPability measure for Adults (ICECAP-A).^52^NHS resource use via a study specific questionnaire.

The following clinical data will be collected baseline, 6, 12 and 15 month time-points:

Anthropometrics, including height, weight, BMI, abdominal waist circumference.Body composition, assessed with dual-energy X-ray absorptiometry (DEXA).7 day blood pressure diary.Cardiopulmonary fitness assessed by cardiopulmonary exercise testing (CPET).

The following clinical data will be collected at 0, 6 and 12 months only:

CTCA coronary angiography, enabling analysis of luminal stenosis, plaque volume (subdivided by composition), FAI and coronary flow change (assessed by CT-derived fractional flow reserve (FFR_CT_)).Fasting blood tests measuring full lipid profile, glucose, glycated haemoglobin (HbA1c) and inflammatory markers (eg, high-sensitivity C-reactive protein).Cardiac structural and functional assessment with echocardiography.

The following free-living data will be collected at baseline, 6, 12 and 15 month time points:

7 day photographic and/or written diet diary, to track change in dietary patterns over time.7 day physical activity monitor (GENEActiv) to characterise free-living physical activity.

In line with the objectives of a feasibility study, we will also gather information on:

Recruitment and dropout rates.Adherence to SR, assessed via attendance, maximum rating of perceived exertion (RPE) during HIIT, and proportion of participants opting for virtual dietary sessions.A qualitative assessment of trial procedures and SR acceptability via interim and end-of study interviews with participants and practitioners. (figure 2)

**Figure 2 F2:**
[figure not shown]
Study assessment and intervention timeline. BP, blood pressure; CPET, cardiopulmonary exercise test; CTCA, CT coronary angiohgraphy; DEXA, Dual-energy X-ray absorptiometry.

### Cardiopulmonary exercise testing (CPET)

Participants in both groups will undergo a symptom-limited CPET to determine their VO_2_peak and maximum heart-rate, which will guide exercise intensity parameters for SR HIIT sessions. The CPET will be conducted on a cycle ergometer, beginning with a 5 min warm-up against zero resistance. A subsequent ramp progression is used with resistance increasing by 10–20 watts-per-minute (individualised to participant) aiming for a total duration of 8–12 min.^53^ The test discontinues at volitional exhaustion targeting a Borg rating of perceived exertion (RPE) of ≥17. A subsequent recovery phase lasts≥3 min against zero resistance. Achievement of VO_2_peak will be assumed if the following criteria are met:^53^

Respiratory exchange ratio≥1.10.orIncrement in VO_2_≤5 mL/kg^−1^.min^−1^ in response to increasing gradient.andRPE ≥17.

Participants unable to complete the CPET due to a health problem raised during the exercise test or concerning discomfort exercising will discontinue involvement in the study on safety grounds. Participants who achieve an RPE<19 and a maximum heart-rate<80% of their age-predicted will be invited for a repeat test to confirm the accuracy of results.

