### Randomisation

Following completion of all baseline assessments, participants will be block randomised (1:1) to SR and Usual Care or Usual Care only. Randomisation will be performed using a web-based platform (Sealed Envelope: https://www.sealedenvelope.com/) in permuted blocks of four with stratification by sex using an allocation sequence generated at random.

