#### Success criteria

Feasibility will be assessed against the following success criteria:

Recruitment rate: ≥40% of invited eligible participants consent to participate.Retention: ≥70% of participants complete the study.Intervention adherence: ≥70% of SR participants complete≥75% of sessions.Intervention acceptability: ≥70% of participants consider SR acceptable.Streamlined criteria correctly captures >90% of patients with MetS. If this is <90%, we will examine whether any other combination of measures would be more predictive.Quantitative data collection methods are feasible and acceptable to participants and no substantive issues identified within patient-reported/qualitative data that contraindicate progression to RCT.Successful testing of the proposed cost-effectiveness framework and data collection facilities.Preliminary data for CAD regression to guide power calculations for subsequent RCT.

Criteria 1–5 will be based on the lower 90% confidence limit (CL). For example, success criteria 1 will be met if the lower limit of the 90% exact binomial CI for the recruitment rate is ≥ 40%. Progression to a full trial will be considered if these criteria are met. If any of the progression targets are not met but fall between 60% and 100% of the target (eg, having a lower CL for recruitment rate between 24% and 40%) then reasons for this would be considered by the trial management and advisory groups, which may result in changes being made to the trial design for the full trial. If any of the criteria fell below 60% of the target (eg, a lower CL for recruitment rate of less than 24%), then progression would not occur without significant and evidence-based changes to design.

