### Trial management

#### Study governance

The trial management group (TMG) will be led by the cochief investigators and include the full research team. The TMG will be responsible for overseeing the day-to-day running and management of the trial.

One independent trial advisory group (TAG) will fulfil the roles traditionally undertaken by the trial steering committee and data monitoring committee. It will comprise of an independent cardiologist, health economist, CR nurse and a patient representative. TAG will be consulted for advice (eg, regarding decisions for specific study procedures and processes, including adverse events), and will meet at the beginning, mid-point and end of the study, helping to prepare for a subsequent multicentre RCT.

Adverse events (AEs) and serious AEs (SAEs) will be recorded throughout the study, up to and including final follow-up. Review of AEs will take place during TMG meetings, discussed with the TAG and reported to the sponsor and research ethics committee in line with their guidelines.

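### The CPET discontinuation rule names no visit; if it is applied after randomisation, it removes randomised participants for health-related reasons and counts them as retention failures

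*Protocol article*

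**What the plan says.** All places are in the protocol article.

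- **Cardiopulmonary exercise testing (CPET).** The test applies to both arms: "Participants in both groups will undergo a symptom-limited CPET". The rule is triggered by specific causes and not by every incomplete test: "Participants unable to complete the CPET due to a health problem raised during the exercise test or concerning discomfort exercising" is the group concerned, and they "will discontinue involvement in the study on safety grounds". What ends is involvement in the study, not only the test or the exercise programme. No visit is named.
- **Assessments.** One list is introduced by "The following clinical data will be collected baseline, 6, 12 and 15 month time-points" and includes "Cardiopulmonary fitness assessed by cardiopulmonary exercise testing (CPET"). CTCA, fasting bloods and echocardiography are in a separate list, at 0, 6 and 12 months only.
- **Randomisation.** "Following completion of all baseline assessments, participants will be block randomised (1:1"). A failed baseline CPET therefore precedes randomisation, and a failure at any later test follows it.
- **Study objectives and Success criteria.** Retention is the proportion who complete the study, with the target "Retention: ≥70% of participants complete the study". The target is judged on the lower limit of a 90% exact binomial interval.
- **Study governance.** "Adverse events (AEs) and serious AEs (SAEs) will be recorded throughout the study, up to and including final follow-up".

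**The concern.** Read literally, the rule covers any scheduled CPET. At 6, 12 or 15 months it would take a randomised participant, in either arm, out of the study because of a health problem or discomfort on exertion. Three things would follow.

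1. **Informative loss.** The reason for removal is tied to the participant's cardiac health or fitness, and so plausibly to later CTCA, fitness and symptom data. It could differ between arms, because only one arm trains at high intensity. Change in CAD is meant to inform the power of the future trial, and it would be estimated in a selected sample.
2. **A retention figure with two meanings.** Removals required by the protocol would be pooled with participants who chose to leave or were lost, although the two call for different responses when the full trial is designed.
3. **Unclear safety follow-up.** The article does not say how ending involvement fits with AE recording up to final follow-up.

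The rule also reaches usual-care participants, who receive no supervised high-intensity sessions.

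**Working it through.** **Check of the interval method.** The article names the exact binomial method (Statistical analysis) and gives two intervals for 25 participants (Sample size). With x successes in n, the exact 90% limits are the 5% quantile of Beta(x, n−x+1) and the 95% quantile of Beta(x+1, n−x).

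- 16/25 = 64%: 45.6% to 79.8%. The article gives 46% to 80%.
- 21/25 = 84%: 67.0% to 94.3%. The article gives 67% to 93%.

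The lower limits, which drive the success criteria, reproduce. The one-point difference in the second upper limit does not affect this point.

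**Completers needed for retention.** Inputs: N = 50 (Study design), target 70% on the lower 90% limit (Success criteria).

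- 41/50 = 82%: lower limit 70.7%, met.
- 40/50 = 80%: lower limit 68.4%, not met.

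So at least 41 completers are needed, and 50 − 41 = 9 losses from all causes can be absorbed.

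**Middle band.** Success criteria defines it as 60% to 100% of the target: 0.60 × 70% = 42%, so a lower limit from 42% up to 70%. The lower limit is 41.5% for 27/50 and 43.4% for 28/50, so the band is 28 to 40 completers.

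**Effect of the rule on retention.** The article gives neither an expected dropout nor a CPET failure rate, so both are assumptions. Let r be retention without the rule and q the proportion of those participants whom the rule removes. Then p = r × (1 − q), and the chance of meeting the criterion is P(X ≥ 41) with X ~ Binomial(50, p).

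| r (assumed) | q = 0 | q = 4% | q = 6% | q = 10% |
|---|---|---|---|---|
| 85% | 79.1% | 55.9% | 43.7% | 23.1% |
| 88% | 92.9% | 75.9% | 64.0% | 38.9% |
| 90% | 97.5% | 86.6% | 76.7% | 51.5% |
| 95% | about 100% | 98.9% | 96.3% | 82.0% |

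For r = 88% the values of p are 0.880, 0.845, 0.827 and 0.792.

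**What q means per test.** An assumed 2% removal at each of two tests gives q = 1 − 0.98² = 4.0%; at each of three tests, q = 1 − 0.98³ = 5.9%. With r = 88% the chance of meeting the criterion is then 76% and 65%. The two-test figure matters because a participant who fails at 15 months, the last scheduled visit, has almost finished and might be counted as a completer.

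**Where a miss would land.** Even with r = 88% and q = 10%, P(X ≤ 27) is below 0.01%. Almost every miss would fall in the middle band.

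**Which CTCA data are exposed.** Scans are at 0, 6 and 12 months.

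| CPET failed at | CTCA lost |
|---|---|
| Baseline | Not a post-randomisation loss |
| 6 months | 12-month scan; possibly the 6-month scan, if CPET comes first |
| 12 months | 12-month scan only if CPET comes first; the text does not give the order |
| 15 months | None |

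**The case against.** The strongest reply is that the rule was meant for the baseline test only. The CPET paragraph introduces the test as the guide to exercise intensity in the intervention, which is a pre-training function. The exclusion criteria already rule out people who cannot exercise, so a baseline test that reveals this would act as an eligibility check. On that reading no randomised participant is lost and none of these consequences arises. This reading is plausible, but the text does not state it. The article repeats the CPET three times after randomisation, and two centres could apply the sentence differently.

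Other replies also carry weight:

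- Every rate above is assumed. If underlying retention is 95%, removal of 4% or 6% changes little.
- Missing 41/50 does not stop progression. It brings the result to the management and advisory groups, who would consider the reasons.
- Retention is defined as completing the study, not as willingness to stay. If the full trial kept the rule, these losses would be real and should be counted. That supports reporting them separately rather than leaving them out.
- The study does not aim to determine efficacy, so selection in the CAD data affects planning inputs only.
- A condensed article may leave withdrawal procedures to the full protocol. Here, however, it states a rule outright, and that rule's scope is unclear against its own visit schedule.

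A reader might also infer that AEs after a worrying test would go unrecorded. The article does not say so. The Study governance section can equally be read as still applying to these participants, so this is a point to clarify, not an established conflict. Nor does the text support reading the rule as covering anyone who fails to finish a CPET for any reason.

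**Conclusion.** The point stands as an ambiguity with real consequences on one of its two readings. It is not an established defect. If the rule applies only at baseline, there is no effect after randomisation. If it applies at follow-up, the direction is clear: loss related to health, and a lower retention figure. The size is not known, because the article gives no CPET failure rate or expected dropout. At an assumed 88% underlying retention, removal of an assumed 4% to 10% lowers the chance of meeting the criterion from 93% to between 76% and 39%.

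Two stronger readings should be avoided. One is that the rule would block the full trial: a miss would most likely prompt review. The other is that it puts all the CAD data at risk: the 6-month test clearly threatens the 12-month scan, the 12-month test may do so, and the 15-month test cannot.

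The change is still worth making, because it is cheap and protects the data intended for planning the next trial.

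**What to change.** Reconcile the CPET, Assessments, Randomisation, Success criteria and Study governance sections as follows:

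1. State which CPET visits the discontinuation rule covers.
2. Separate stopping exercise testing or training from stopping data collection. The former stays with the existing clinical safety judgement and is not altered here.
3. For randomised participants, continue the non-exercise data collection already scheduled (CTCA, questionnaires, bloods, AE recording) where consent continues and the clinician sees no safety objection. Record the CPET as not completed, with the reason.
4. In the retention result, report CPET-triggered discontinuations by arm and separately from voluntary dropout, and state how they count towards the 70% criterion.

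The cost is a few sentences of clarification, handled as a protocol amendment if the sponsor judges one necessary, and one extra line in the retention table. The visits and assessments are already scheduled. If the intent was baseline only, saying so settles item 1 and leaves the others as a short statement of how follow-up is handled.

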### Control arm: usual care

All patients will be offered guideline-based recommended doses of aspirin and statin, unless contraindicated.^54 55^ Participants’ general practitioners will be provided with a study information sheet and encouraged to adjust medications as needed according to national guidelines (eg, for hypertension) if conditions change while participating in the study. Participants will also be provided routine, verbal one-off lifestyle advice in line with NICE guidance, recommending 150 min of moderate intensity exercise per week, encouraging a healthy, balanced diet, weight loss, reducing alcohol consumption and smoking cessation.

### Intervention arm: Super Rehab (plus usual care)

A detailed description of the SR protocol is provided in the online supplemental material. In short, SR is designed to enable and support successful behavioural change with a predominant focus on exercise and diet, with all sessions delivered 1-to-1. The programme will be explicitly introduced by a cardiologist, ensuring the programme is presented as a meaningful intervention to improve health outcomes. The cardiologist will introduce the concepts involved in the nutritional advice, provide advice and oversight to both the dietitian and exercise trainers, and conduct a further clinical review at the end of each intervention phase.

10.1136/bmjopen-2023-080735.supp1Supplementary data

SR has three phases: (1) *introduction*, (2) *developing* and (3) *maintaining* (outlined in figure 3). Practitioners will use autonomy-supportive behavioural techniques, including action planning, goal setting and self-monitoring.^28 30^ This will include frequent measurement of body metrics (blood pressure, heart-rate, BMI) to enable goal-setting and biofeedback to encourage adherence. The exercise component will be delivered in local community-based exercise facilities, with the last phase offered virtually if preferred. The dietary component will either be face-to-face or virtually according to individual participant preference.

**Figure 3 F3:**
[figure not shown]
The Super Rehab programme.

Supervised exercise session will be split between HIIT, using the Norwegian 4×4 model for CAD patients,^22^ and resistance training. Participants will be set weekly homework exercise to do by their exercise trainer. This will comprise moderate-intensity aerobic exercise for 45 min in *introduction* and *developing* phases, and increase to higher-intensity exercise in the *maintaining* phase. A once weekly resistance exercise session using workouts learnt in the supervised session during *introduction* and *developing* will be added in the *maintaining* phase.

Dietary support will consist of 1:1 sessions with a dietitian who will work with patients using pre-session combined photographic/written diet diaries to identify incremental areas of improvement in a straightforward manner. A SR introductory educational booklet incorporating diet structure will be provided. Recognising that there is no ‘one-size-fits-all’ pattern, the dietitian will work with the patient to identify residual barriers to dietary change and potential solutions and, where indicated, continue to highlight the importance of smoking cessation. SR manuals will be provided to exercise trainers and dietitians to support the delivery of a consistent programme across centres and practitioners.

### Data analysis plan

#### Data collection

##### Qualitative

SR participants will be contacted by phone for short interim acceptability assessments at the end of ‘introduction’ and ‘developing’ phases. On completion of the study, a full interview will capture all ranges of experiences. This will seek feedback on trial participation, including barriers and facilitators to trial procedures, adherence and explore any unanticipated effects of taking part. Usual care participants will be invited for a short phone call to discuss their experience of trial participation. Encrypted interviews will be recorded, transcribed verbatim (by an external transcription company) and analysed using both narrative and thematic analysis.^56^ Anonymised patients who decline the interview will be asked a very brief set of questions on reasons for refusal.

In-depth interviews will be conducted with all practitioners involved in delivering SR to identify areas that need to be adapted or changed to implement the intervention in a future trial. Specifically, this will include their experience of delivering and supporting SR, the quality of the training resources and how participation affected their other work and relationships with patients.

##### Health economics assessment

This study will consider the feasibility of collecting the data needed for a full health economic analysis in a subsequent RCT. The primary perspective will be the NHS and personal social services,^57^ but data will also be collected on costs incurred by patients. Training-related costs for participating staff and intervention activity data will be recorded by staff delivering SR using a study-specific form. At each assessment, patients will be asked to supply data on resource use via a questionnaire based on the Client Service Receipt Inventory.^58^ Resource use data will be costed using national sources (eg, National Tariffs and Formulary). The EQ-5D-5L data provides the basis for calculating quality-adjusted life-years (QALYs) specified by NICE for use in the subsequent cost utility analysis.^51 57^ The ICECAP-A capability measure provides a complementary assessment of quality-of-life that could provide additional insight into the impact of SR on patients’ outcomes in subsequent economic evaluation.^52^

#### Data management

Once collated, all data will be stored and analysed pseudonymously using a unique identifier code. An electronic cross-referencing list will be stored on an NHS password-protected computer database at each study site. Only pseudonymised data using the unique identifier code will be used on data sets shared with external collaborators. All research records will be destroyed after 10 years.

CTCA artificial intelligence imaging techniques used in the study require image transfer off-site for analysis. For FAI analysis, images will be transferred to the Oxford Translational Cardiovascular Research Group core laboratory at the University of Oxford. We will use the existing pathway for pseudonymised image transfer via the study sponsor’s collaboration with the University of Oxford on The Oxford Risk Factors And Non Invasive Imaging Study (ORFAN), which has separately been approved by the South Central—Oxford C—Research Ethics Committee (Reference 15/SC/0545). For participants recruited at North Bristol NHS Trust, all acquired CT imaging will also be pseudononymised and transferred via PACS to the sponsor for analysis, and to Caristo (company providing FAI analysis for non-ORFAN sites). For FFR_CT_ analysis, images will be sent to HeartFlow, who’s core laboratory (California, USA) provide this analysis for NHS hospitals in standard clinical care. Existing secure information sharing protocols for standard clinically indicated scans will be used for image transfer.

#### Blinding

The nature of the intervention (SR) prevents blinding of the participants and clinicians to their trial arm. However, statistical, health economic and clinical outcome analyses (including CTCA (FAI, FFR_CT_, stenosis) and blood results) will be completed blinded to study allocation.

#### Statistical analysis

Feasibility measures will be reported with 90% CIs calculated using the Exact Binomial Method; 90% intervals are chosen (rather than 95%) because the upper limits of these measures are not of direct interest for evaluating feasibility.

For the SR group, the proportion of participants adequately completing the intervention and the average number of supervised exercise and nutritional sessions completed will be reported (by intervention phase). The number and proportion of virtual sessions opted for will also be reported. A quantitative analysis of exercise intensity and nutritional change achieved with SR will be undertaken.

The distributional properties of the continuous variables will be examined by plots. Participant characteristics and outcomes will be summarised using descriptive measures: mean (SD) or median (IQR) for symmetric or skewed continuous variables, respectively; number (percent) for categorical variables; and mean (SD) absolute and percent change for longitudinal data will be reported separately by treatment allocation. Linear regression analysis of the preliminary data for CAD regression will support power calculations for subsequent RCT. Summary statistics, including missing data, for baseline and follow-up cost data will be reported.

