### Inclusion criteria

Aged 18–75 years at consent.CTCA demonstrates CAD with plaque causing a stenosis of ≥25% in ≥1 coronary artery.Evidence of coronary inflammation (FAI>−70.1 HU or FAI-score (relative to age-matched and sex-matched patients) ≥75th percentile in the left anterior descending or right coronary artery or ≥90th in the circumflex^35^).MetS, defined as ≥3 of the following within 6 months of CTCA^44^High abdominal waist circumference (≥94 cm males, ≥80 cm females).Hypertension (≥130/85 mm Hg or on treatment).Diabetes mellitus or raised fasting glucose or HbA1c (glucose≥5.6 mmol/L, HbA1c≥42 mmol/L).Reduced high-density lipoprotein (≤1 mmol/L males, <1.3 mmol/L females).Raised triglycerides (>1.7 mmol/L).

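### Percent change is planned for all longitudinal outcomes, but it reverses sign for FAI and is undefined for any plaque component that is zero at baseline

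*Protocol article*

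**What the plan says.** The rule for change over time is in the Statistical analysis section: "mean (SD) absolute and percent change for longitudinal data will be reported separately by treatment allocation". It names no exception and gives no formula for percent change. Earlier in the same sentence, continuous variables are to be summarised by "mean (SD) or median (IQR) for symmetric or skewed continuous variables, respectively", but the clause on change names only mean (SD).

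The Assessments section brings two relevant outcomes under the rule. It lists "plaque volume (subdivided by composition), FAI and coronary flow change" among the CTCA measures, under the statement "The following clinical data will be collected at 0, 6 and 12 months only". FAI and the plaque components are therefore longitudinal data.

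The Inclusion criteria show the scale and direction of FAI: "Evidence of coronary inflammation (FAI>−70.1 HU or FAI-score (relative to age-matched and sex-matched patients) ≥75th percentile". A higher, less negative value marks inflammation, so improvement is a move to a more negative value. The same section requires that "CTCA demonstrates CAD with plaque causing a stenosis of ≥25% in ≥1 coronary artery". That ensures some plaque at baseline but sets no minimum for any one component.

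On use in the next trial, the Statistical analysis section says: "Linear regression analysis of the preliminary data for CAD regression will support power calculations for subsequent RCT". It does not say whether that regression uses absolute or percent change.

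**The concern.** Percent change is meaningful when a variable is positive and its zero means that nothing is there. FAI meets neither condition. With a negative baseline in the denominator, an improvement appears as a positive percentage and a deterioration as a negative one. The absolute and percent columns for the same outcome would then point in opposite directions.

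Plaque components are non-negative and have a true zero, but a given component may be absent or nearly absent at baseline. Percent change then has no value, or takes one so large that a single participant governs the mean and SD of an arm of about 25.

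What is at stake is the readability of the descriptive tables and, at one remove, the choice of SD for planning the next trial. The abstract and the Study objectives both intend the CAD change data for that purpose, and a planner who took the SD of percent change from such a table could be misled.

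**Working it through.** **Inputs.** From the protocol: FAI cut-off −70.1 HU, with higher values marking inflammation (Inclusion criteria); 25 participants per arm (Sample size); mean (SD) of absolute and percent change (Statistical analysis). All other baseline and follow-up values below are assumed for illustration, since the article gives no FAI or plaque data.

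**Formulas.** Absolute change = follow-up − baseline. Percent change = 100 × (follow-up − baseline) / baseline. This is the ordinary definition; the protocol gives no other.

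**Step 1: sign for FAI.**
- Improvement, −70.1 to −75.1 HU: absolute −5.0 HU; percent 100 × (−5.0)/(−70.1) = +7.1%.
- Deterioration, −70.1 to −65.1 HU: absolute +5.0 HU; percent 100 × (+5.0)/(−70.1) = −7.1%.

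The reversal follows from the negative denominator, so it occurs at every negative baseline.

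**Step 2: does dividing by |baseline| repair it?** It repairs the sign: 100 × (−5.0)/70.1 = −7.1%. It does not give the percentage a meaning. The same 5 HU fall is 5/60 = 8.3% from −60 HU and 5/90 = 5.6% from −90 HU, so the participant with the higher FAI scores the larger percentage for an identical change. Moving the origin of the scale by 1,000 units turns a baseline of −70.1 into 929.9. The absolute change stays at −5.0, but the percent change becomes −5.0/929.9 = −0.54%. Where zero is placed decides the answer.

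**Step 3: plaque components.** Volumes in any one unit:
- 0 to 5, or 0 to 0: division by zero, no value. Absolute changes are +5 and 0.
- 1 to 6: +500%. Absolute change +5.
- 0.1 to 5.1: +5000%. Absolute change +5.
- 50 to 55: +10%. Absolute change +5.

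**Step 4: effect on an arm's summary.** Take five participants with baselines 1, 50, 60, 80, 100 and follow-ups 6, 45, 54, 72, 90.
- Mean absolute change = (5 − 5 − 6 − 8 − 10)/5 = −4.8.
- Total volume goes from 291 to 267, a fall of 24/291 = 8.2%.
- Mean percent change = (500 − 10 − 10 − 10 − 10)/5 = +92%.

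At the planned arm size, let 24 participants fall by 10% and one rise from 1 to 6:
- Mean percent change = (24 × (−10) + 500)/25 = 260/25 = +10.4%.
- Sum of squares = 24 × (−20.4)² + 489.6² = 9,987.84 + 239,708.16 = 249,696.
- SD = √(249,696/24) = 102 percentage points.

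Regression in 24 of 25 participants would be shown as average progression. This shows what can happen. It does not estimate how likely it is.

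**The case against.** The strongest reply is that little depends on this column. Absolute change is reported beside percent change, so a reader who sees −5.0 HU is unlikely to mistake the direction. The study is not designed to determine efficacy. Under Success criteria, criteria 1–5 are judged on the lower limit of a 90% exact binomial interval, and the criterion on CAD regression asks only for preliminary data to guide power calculations. All of this stands, and it makes the point minor.

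A second reply is that the formula and a rule for zero baselines may be in a statistical analysis plan that is not shown. That is fair, and their absence from an article is not the complaint. The article does state a rule that covers FAI and the plaque components without exception, and for FAI no choice of denominator makes percent change meaningful (Step 2).

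A third reply is that change can be roughly symmetric even when levels are skewed, and that a later power calculation needs the SD of change. This also stands. Mean (SD) of absolute change is a reasonable default, and the median rule is needed only where change itself proves skewed.

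Three stronger readings are tempting but unsupported:
- A reader might infer that percent change will distort the planning of the next trial. The documents assign that role to a linear regression whose scale is not stated, and the abstract speaks only of variance of change in CAD. The introduction also describes FAI as a marker of inflammation, while its account of regression concerns plaque.
- A reader might infer that participants will be dropped, or means inflated. The documents give no distribution of plaque components and no rule for excluding anyone, so the frequency is unknown.
- A reader might extend the point to questionnaire scores that could be zero. The article does not give their scoring, so the point is confined to the CTCA outcomes.

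**Conclusion.** The point holds as a minor correction to a descriptive summary. For FAI, the percent change required by the stated rule has the opposite sign to the absolute change (±5.0 HU from −70.1 HU becomes ∓7.1%), and taking |baseline| leaves a figure without a fixed meaning. For plaque components, percent change is undefined at a zero baseline and unstable near zero.

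The FAI conclusion assumes negative baseline values, as the cut-off suggests; the sign reversal also assumes the ordinary signed denominator. The plaque conclusion is conditional on zero or near-zero components occurring, and the documents do not show how often they do. Total plaque volume is not affected by the zero-baseline problem, because eligibility requires plaque. No feasibility conclusion or progression decision changes.

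**What to change.** Amend the clause on change in the Statistical analysis section:
- Report FAI as absolute change in HU only.
- Report each plaque component as absolute change, using median (IQR) where the change is skewed, in line with the rule the plan already applies to continuous variables.
- Restrict percent change to positive variables with a true zero, for example total plaque volume.
- State that the SD of change taken to the power calculation for the next trial is that of absolute change.

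The cost is a sentence or two of wording, with no new data, visits or participants. The downside is the loss of a percent column for FAI and the plaque components, which some readers may expect for comparison with other imaging studies.
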